## Abstract

**Context:** Internet Use Disorder (IUD), characterized as the inability to control one's internet use, is emerging as an increasing societal concern as it is associated with reduced quality of life and mental health comorbidities. Evidence-based treatment options are, however, scarce due to the novelty of the diagnosis. Internet- and mobile-based interventions may be an effective means to deliver psychological treatment to individuals with IUD as they address individuals affected in their online setting. The aim of the study is to evaluate the efficacy of a newly developed, guided internet- and mobile-based intervention for IUD.

**Methods:** In a two-armed randomized controlled trial (*N* = 130), individuals showing problematic internet use patterns (Internet Addiction Test ≥ 49) will be randomly allocated to the internet- and mobile-based intervention or a waiting control group. Assessments will take place at baseline, 7 weeks, 6- and 12 months after randomization. The primary outcome is internet addiction symptom severity (IAT) at 7 weeks. Secondary outcomes include quality of life, depressive symptoms, anxiety, and other psychosocial variables associated with IUD.

**Intervention:** The intervention consists of seven sessions: Goal setting and motivational interviewing, impulse control, problem solving, cognitive restructuring, self-worth, relapse prevention, and a booster session. Participants are supported by an eCoach who provides individual feedback after completion of each session. Participants can choose between several elective sessions based on individual need.

**Conclusions:** This is the first study to evaluate an internet- and mobile-based intervention for IUD, which could be a promising first step to reduce individuals' disease burden.

**Trial Registration:** DRKS00015314.

The study is currently ongoing. First participants were enrolled in the study on September 14th 2018. Recruitment will continue approximately through March 2020.

## Introduction

Internet Use Disorder (IUD) is characterized by excessive or poorly controlled preoccupations, urges, or behaviors regarding computer use and internet access that lead to social or work-related impairment or distress (1). It includes both excessive gaming and non-gaming internet activities. Non-gaming internet activities can be differentiated in internet gambling, internet pornography, information overload (obsessive research and surfing), internet compulsive buying (2), and excessive social media use. (3, 4). Surveys have indicated that IUD affects 1.5–8.2% of the general population (1, 5). IUD prevalence rates are, however, highly inconsistent due to the varying definitions.

Individuals with IUD show significant social, physical, and mental burdens. IUD may also cause neurological complications, psychological distress, and social problems (6–8). In addition, high comorbidity with psychiatric disorders have been reported, especially affective disorders, anxiety disorders, impulse control disorders, substance use disorders, and attention deficit hyperactivity disorder (1, 9–11). Impairment caused by IUD has also been found to include educational failure, reduced academic perspectives (12, 13), and functional impairment (14).

Despite the severe burden of disease, the range of available specialized evidence-based treatment options for IUD is extremely rare. Treatment accessibility for IUD is impeded as it has only been unsystematically treated so far by selected addiction counseling or educational counseling (15). Currently, there are only very few empirical studies evaluating IUD treatment approaches meeting the scientific standards for randomized controlled trials (16). It has been shown that cognitive-behavioral treatments have large and robust effects on the symptoms of IUD, outperforming other treatments. Among the researched psychological treatments for IUD, none of them measures the effect of an internet-based treatment approach (16). Low utilization of treatment is caused not only by structural but also attitudinal barriers such as fear of stigmatization and low outcome expectancies (17, 18). Internet- and mobile-based interventions can offer a possibility to deliver specialized treatment with a low threshold for uptake.

Treating IUD via the internet may appear contradictive at first. However, there are many arguments supporting this approach: (1) Reaching the target group through their common online setting could be effective as the internet is easily accessible and attractive. (2) Since the target group usually shows low levels of treatment motivation (19), an easily accessible and attractive treatment option is crucial; thus, a low-threshold intervention with interactive audio-visual content may facilitate access and reduce burdens of help-seeking. (3) Due to the individually tailored and adaptable content, a variety of symptoms associated with IUD such as procrastination, bad sleep patterns or alcohol consumption can be addressed. Based on these comorbid symptoms, secondary outcome measures were chosen to assess a reduction in symptoms associated with IUD that were targeted in the intervention. (4) Internet- and mobile-based interventions might be a feasible means to provide evidence-based treatment on a large-scale basis, since they have been shown to be effective in the treatment of numerous mental health disorders (20–23). Therefore, internet- and mobile-based interventions could be a way to reach individuals with IUD better than traditional approach. To the best of our knowledge, this is the first trial evaluating a guided internet- and mobile based intervention for IUD in an RCT design.

## Aims of the Study

The aim of this study is to evaluate the efficacy of a cognitive-behavioral guided self-help internet- and mobile-based intervention for reducing symptoms of IUD compared to a waiting control group (WCG). Both groups have unlimited access to treatment as usual in routine mental health care. It is hypothesized that the intervention reduces symptoms of IUD.

## Methods

### Design

A two-arm randomized controlled trial (RCT) will be conducted to evaluate the internet- and mobile-based intervention compared to a WCG. Assessments will take place at baseline (t1), post-intervention (t2), at 6- (t3) and 12-months follow-up (t4). See Figure 1 for a detailed overview of the study design. All procedures involved in the study will be consistent with the generally accepted standards of ethical practice approved by the Friedrich-Alexander University of Erlangen-Nuremberg ethics committee (54_18 B).

**Figure 1 F1:**
[figure not shown]
Study flow chart.

### Participants and Procedures

#### Inclusion and Exclusion Criteria

We will include individuals who (1) are at minimum 18 years of age, (2) show elevated levels of IUD with scores of ≥ 49 on the Internet Addiction Test (IAT) (7), (3) have internet access, (4) have sufficient German language reading and writing skills and (5) are willing to give informed consent. We will exclude subjects who (1) indicate that they have been diagnosed with a psychosis or bipolar disorder, (2) show a notable suicidal risk as indicated by a score greater than 1 on Item 9 of the Beck Depression Inventory (BDI) (24), (3) currently receive or are on a waitlist for psychological treatment regarding any mental disorder.

#### Recruitment

Participants will be recruited in Germany, Austria and Switzerland via (1) the GET.ON Website, (2) the StudiCare website, (3) recruitment over social media and discussions forums, and (4) mass e-mailing with information regarding the study and intervention sent to German, Swiss and Austrian psychological counseling centers and university students (in Erlangen, Ulm, Bern, Dresden, Hagen and Vienna).

#### Assessment of Eligibility and Randomization

After registering with a self-chosen email address, applicants will receive an email with detailed information about the study procedure. They will be further informed that it is possible to withdraw from the intervention and/or study at any time without any negative consequences. Applicants are asked to complete an online screening questionnaire and to sign the informed consent form and return it by post or email. As soon as participants have completed the baseline assessment and meet the inclusion criteria, they will enter the study and will be randomized to one of the two study conditions. Participants are randomized to either the guided intervention group or a WCG in a 1:1 ratio. Randomization is performed by a research assistant not otherwise involved in the study using block randomization with varying block sizes. Once randomization has been completed, participants in the intervention group receive immediate access while participants in the control group receive access 12 months later.

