### Intervention

The intervention consists of seven sessions: Goal setting and motivational interviewing (session 1), impulse control (session 2), problem solving (session 3), cognitive restructuring (session 4), self-worth (session 5), relapse prevention (session 6), and a booster session 4 weeks after completion of the core sessions (session 7) (see Table 1 for an overview of the main sessions). Moreover, participants can choose between several elective sessions based on individual need and preference. The elective sessions are directed at personal needs and values, sleep, relaxation, alcohol and affect regulation, appreciation and gratefulness, and procrastination (see Table 2 for an overview of the elective sessions). Each session can be completed in ~30–45 min. We advise participants to do at least one and a maximum of two sessions per week. Further content can only be accessed once previous sessions are completed. Consequently, the training will last about 4–6 weeks plus one additional booster session 4 weeks after completion of the last session. The booster session aims to help participants to refresh and reflect contents and strategies. Sessions consist of texts, testimonials, and include many interactive elements such as quizzes, exercises, and homework, which can be seen in the Supplementary Material. At the end of the second session, a plan for behavior change is introduced. This four-step plan aims to help participants to (1) choose specific situations in which they want to change their internet use, (2) set realistic goals, (3) collect ideas on how to realize their goals, and (4) to create a detailed plan for goal acquisition including newly acquired strategies and planning for potential upcoming difficulties. Participants are expected to test their plan for behavior change during the following week and are encouraged to analyze success and difficulties in the training process in the next session. They can also opt to review and adapt their plan in the following session. Participants are encouraged to formulate five plans in total over the course of the training between the second and the sixth session. They are also invited to keep an online diary, which can be accessed via the web interface or an optional smartphone app. The intervention uses content tailoring, thereby engaging the participants by encouraging them to make real-time choices among various response options, and then providing individualized content based on specific needs or preferences. The training is built on responsive web-design and can be completed on any kind on internet-ready device, such as PCs/laptops, smartphones, or tablets. Participants can also opt to receive motivational messages and small exercises referred to as *Tiny Tasks*. These smartphone notifications are sent directly to their mobile device 3 times a day. These notifications will support the participants in transferring the exercises of the training into their daily lives (e.g., giving suggestions on how to implement strategies: “What has influenced your internet usage today?”).

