### Statistical Methods

Data will be analyzed on an intention-to-treat basis including all participants who will be randomly assigned to conditions. Additionally, study completer analyses including only participants who filled out the questionnaires and intervention completer analyses including only participants who have completed at least four out of six sessions will be conducted. Missing data will be handled using multiple imputations (MIs) calculated by a Markov Chain Monte Carlo multivariate imputation algorithm of 100 estimations per missing value. MI is especially robust with respect to missing data. We will conduct an ANCOVA to examine differences in the primary outcome. To detect differences between the two study groups, we will conduct univariate analysis of covariance to compare secondary outcomes at post-treatment and 6- and 12-month follow-up adjusting for baseline scores. Predictors and mediators of changes of the primary outcome will be analyzed on exploratory basis using linear regression. For all analyses on continuous measures, Cohen's d (74) will be calculated by standardizing the differences between baseline and follow-up scores by the pooled standard deviation of the baselines scores.

The response rates will be compared across conditions with the help of contingency tables and Chi-Squared tests. For primary analysis, significance levels will be set at 0.05, one-sided. For the explorative analysis of the data, the significance levels will be set to 5%. All analyses will be performed with IBM SPSS v. 24.

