### Sample Size Calculation

To answer the research question described above, we aim to include 130 participants. That is to statistically detect a medium effect of (Cohen's d) *d* = 0.60, with a power (1–β) of 80% and an α of 0.05 (two-tailed test) for an intention-to-treat analysis using G^*^Power (75). The estimated effect of (Cohen's d) *d* = 0.60 is based on recent meta-analyses on the effects of treatments on internet addiction which shows rather high effect sizes for CBT (16) as well as several other psychological treatments (76).

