
This study also has some limitations. The power analyses was calculated with an estimated effect of *d* = 0.60. It should be taken into account that smaller effects can be clinically relevant as well. We will not include any additional objective measurement of IUD, e.g., tracking of time spent online. To allow a low-threshold approach, only self-reported measurements are used. Future research should consider additional objective measures and independent ratings of internet use and of symptoms associated with IUD. As motivation for treatment is typically low in the target group and guided internet- and mobile-based interventions require high levels of self-regulation, we account for drop-out with a systematic adherence protocol including reminders via email after 7, 14, and 21 days in case participants do not complete a measurement point followed by telephone calls. Moreover, we provide monetary incentives for completing the online questionnaires. With regard to the pitfall of a usually overeducated sample of participants in internet- and mobile-based interventions, we aim to recruit at a broad level in the population, including health insurance companies, counseling centers and local community centers.

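### Control access and the 12-month questionnaire share one nominal date with no stated link, so late control answers can follow use of the training and dilute the secondary 12-month comparison

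*Protocol article*

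**What the plan says.** Four statements in the protocol article bear on this point.

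- **Access.** Assessment of Eligibility and Randomization: "participants in the intervention group receive immediate access while participants in the control group receive access 12 months later". The rule is elapsed time, with no condition attached.
- **Due date of T4.** Abstract: "Assessments will take place at baseline, 7 weeks, 6- and 12 months after randomization". Assessment and Data Management likewise puts T4 at 12 months.
- **Chasing of overdue questionnaires.** The limitations paragraph of the Discussion describes "reminders via email after 7, 14, and 21 days in case participants do not complete a measurement point followed by telephone calls". No closing date is given. This is separate from the session reminders under Guidance, which concern progress through the training.
- **Use of T4.** Statistical Methods plans covariance analyses to "compare secondary outcomes at post-treatment and 6- and 12-month follow-up adjusting for baseline scores". Table 3 schedules twelve outcome scales, including the IAT and CIUS, and the TiC-P cost questionnaire at T4.

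The main endpoint lies elsewhere: "The primary outcome is internet addiction symptom severity (IAT) at 7 weeks".

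**The concern.** A waiting control group is held for a full year so that the 12-month comparison stays a comparison of treated with untreated participants. Here the wait ends on the day the last questionnaire falls due, while the trial goes on asking for that questionnaire for at least 21 more days. A control who answers promptly is untreated. One who answers after the third e-mail or a telephone call may have had the training open for three weeks or longer. Both count as waiting controls in the T4 analysis.

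This can happen in one arm only, because the intervention arm has had access since randomization. If the intervention works, treated controls improve and the difference between arms shrinks. The more successful the reminders are, the more such answers are collected. At stake are the 12-month secondary outcomes and the cost data, and with them what the trial can say about whether benefit lasts.

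**Working it through.** **1. Timing.** With randomization as time zero, control access opens at 12 months and T4 is due at 12 months. E-mail reminders follow at 12 months plus 7, 14 and 21 days, and telephone calls come after that. On the text as written, an answer prompted by the last e-mail comes at least 21 days after access.

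**2. Possible exposure by then.** The Intervention section says: "We advise participants to do at least one and a maximum of two sessions per week".

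- At that pace, 21 days is 3 weeks, so 3 × 1 = 3 to 3 × 2 = 6 sessions.
- The same section puts the training at about 4-6 weeks. Six core sessions over that time give 6 × 3/6 = 3 to 6 × 3/4 = 4.5 sessions in three weeks.
- After only the first reminder (7 days) the figure is 1 to 2 sessions.

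Statistical Methods counts a participant as an intervention completer from four of six sessions. A control who starts at once and answers late could therefore meet the trial's own completer definition.

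**3. Dilution.** Let *f* be the share of control T4 answers given after access, and *g* the share of the full effect gained by then. The control mean moves toward the intervention mean by *f* × *g* of the effect, so

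observed d = d × (1 − f × g).

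The article gives neither *f* nor *g*. The ranges assumed are *f* = 10-30% and *g* = 25-75%. For d, the planning value of 0.60 from Sample Size Calculation is carried over to 12 months, which is a further assumption. With "we aim to include 130 participants" and 1:1 allocation there are 65 controls, so *f* corresponds to 6.5 to 19.5, or about 7 to 20 people.

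Power below is for a two-sided t-test at 0.05 with 65 per arm, all analysed. Without dilution it is 92.4%.

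| f | g | f × g | observed d | power |
|---|---|---|---|---|
| 10% | 25% | 2.5% | 0.60 × 0.975 = 0.585 | 91.1% |
| 10% | 50% | 5% | 0.60 × 0.95 = 0.57 | 89.7% |
| 20% | 50% | 10% | 0.60 × 0.90 = 0.54 | 86.3% |
| 30% | 50% | 15% | 0.60 × 0.85 = 0.51 | 82.3% |
| 30% | 75% | 22.5% | 0.60 × 0.775 = 0.465 | 74.9% |

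At *f* = 5% and *g* = 25% the loss is negligible (d = 0.593, power 91.8%).

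**4. The plan's own figure.** The article gives no figure for late answers or for the 12-month comparison, so there is none to reproduce on this point. Its total of 130 does not follow from the inputs stated beside it (d = 0.60, 80% power, two-sided 0.05), which give 90 by t-test. That is a separate matter, and the dilution percentages do not depend on it.

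**5. What is not touched.** The 7-week and 6-month assessments fall long before any control has access. Six months plus the reminder cycle is still well short of 12 months.

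**The case against.** The strongest reply is that the article is condensed. Its single clause on access does not give the order of access and T4 within month 12, the flow chart is not shown, and the full protocol may hold access back until T4 is in. This stands as a limit on certainty: a reader might infer that the 12-month comparison is contaminated, and the article does not establish that. It does not remove the point. The article fixes an access rule by elapsed time and a chase that runs past the same date, and the two collide. The same section makes randomization wait for completion of the baseline assessment, so a completion condition could as easily have been written here.

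Three other strong readings also fail.

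- *T4 is the only long-term randomized comparison.* The 6-month follow-up is also randomized and is unaffected.
- *Fading benefit could not be told apart from control exposure.* The IAT is measured in both arms at T2, T3 and T4. Fading would show as worsening in the intervention arm, whereas exposure would show as improvement among late-answering controls, whom platform time stamps, if kept, can identify.
- *Early access takes away controls' reason to answer T4.* The Discussion offers money for completing questionnaires and does not restrict it to one arm. An effect of access on response is possible but not documented.

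It is also fair to say that the size is assumed throughout. Six sessions in three weeks needs an immediate start and the maximum advised pace. The Guidance section describes eCoach support for the treatment arm, and the article does not say whether controls later receive it, so their gain could be smaller. Any bias is toward no difference and would not create a false benefit.

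**Conclusion.** The point holds as a conflict between two stated rules, with a possible rather than demonstrated effect on the data. As written, a control who answers T4 late can already have used the training, and the secondary 12-month between-group comparison can be diluted toward no difference. The primary conclusion at 7 weeks and the 6-month comparison stand regardless.

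The shrinkage is 2.5-22.5% if 10-30% of controls answer after access with 25-75% of the effect gained, and close to nothing if few answer late. These figures rest on assumed shares, on a 12-month effect equal to the planning value, and on access opening at 12 months whether or not T4 has been answered. If the full protocol already makes access wait for T4, one clarifying sentence settles the matter. If it does not, the change is worth making, because it is cheap and the bias falls on one arm only.

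**What to change.** Reconcile the access rule under Assessment of Eligibility and Randomization with the reminder cycle in the Discussion. A control's training should be opened only once their T4 questionnaire is submitted or the T4 reminder and telephone cycle has closed, whichever comes first. This requires a stated end to that cycle.

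For controls already past 12 months, use platform time stamps to flag T4 answers given after the control's first session. Keep those answers in the main intention-to-treat analysis. Add a sensitivity analysis that sets them to missing and imputes them under the multiple imputation already planned in Statistical Methods. Dropping them from the main analysis would discard observed data in one arm only, which is why this belongs in a sensitivity analysis. Report how many answers are flagged, so that readers can see the actual late share.

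The cost is one platform trigger, a sentence each in the access and analysis sections, and one extra analysis. The downside is that controls who do not answer T4 on time wait a few weeks beyond the stated 12 months, which the trial team must be willing to state to participants.
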